### 2.7. Statistical analysis

A statistical analysis plan (SAP) including the list of all tables, listings, and graphs will be issued before the study database lock.

The analysis will assume a progressive (monotonicity) relationship (i.e., any dose above an unsafe dose will also be considered unsafe).

Those patients enrolled in Phase Ib who received a placebo or the selected doses in phase Ib will be combined with Phase IIa patients to increase statistical power. To successfully combine the patients from both study phases, the time between phases is minimal, and the design, the follow-up, and data collection will be strictly the same in Phase Ib and Phase IIa parts of the trial, with the only exception of sequential blood and urine sampling for pharmacokinetics and pharmacodynamics performed only in Phase Ib.

Categorical variables will be summarized with counts and percentages. Continuous variables will be summarized with the mean, the standard deviation, the median, the inter-quartile range, the minimum, and the maximum.

Patient's compliance with eligibility criteria and treatment administration, major protocol non-compliances, patient's withdrawals and the reason for withdrawal (e.g., AE, protocol non-compliance, lost to follow up, failed to return, consent withdrawal, and other reasons) and assignment to each analysis population will be summarized by means of the appropriate statistics.

The main results will be provided with 90% confidence intervals.

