## 2. Methods and analysis

### 2.1. Overall design

The current version of the protocol is the APRIL V5, 11 October 2021. To design this protocol, the SPIRIT reporting guidelines (18) were used.

APRIL is a double-blind, randomized, multicenter, placebo-controlled, Phase Ib/IIa clinical Study designed to assess if the administration of ApTOLL together with EVT in AIS patients with confirmed large vessel occlusion (LVO) who are candidates to receive EVT with or without intravenous (i.v.) thrombolysis, is safe and well tolerated. The study population will be composed of men and non-pregnant women in which ApTOLL can be administered within 6 h from symptom onset. For patients with wake-up stroke, onset time will be considered as the time of symptoms first discovered.

The APRIL clinical trial will be divided into two parts: This is a Phase Ib/IIa clinical trial divided into two parts: the first part (Phase Ib) is a single dose escalation study, and the second one (Phase IIa) is an exploratory study to assess the safety and biological effect of ApTOLL at two different doses.

- Phase Ib (32 patients with AIS): a single dose, i.v. administration (30 min infusion), dose escalation with 4 single dose levels (8 patients/level), randomized (1:3), double-blind, placebo-controlled, in patients with AIS.

- Phase IIa (119 patients): a single dose, i.v. administration (30 min infusion), parallel (3 arms, placebo:ApTOLL dose A:ApTOLL dose B), randomized (√2:1:1), double-blind, placebo-controlled, in patients with AIS.

Therefore, after the completion of Phase Ib a data safety monitoring board (DSMB) unblinded to study groups will select 2 doses (A or B) to be tested in Phase IIa according to initial safety results (Figure 1).

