**Figure 1 F1:**
[figure not shown]
Scheme of APRIL trial. APRIL is divided into two Phases. Phase Ib is a single ascending dose where 8 patients (6 ApTOLL: 2 Placebo) will be enrolled in 4 sequential ascending dose arms (0.025, 0.05, 0.1, and 0.2 mg/kg). After analyzing safety results from Phase Ib, the DSMB will select two doses to be administered in Phase IIa. In Phase IIa three parallel arms (Dose A, Dose B, and Placebo) will be studied. At the moment of this publication, Phase Ib is completed and the doses 0.05 and 0.2mg/kg have been selected to continue during Phase IIa.

The study population will be men and non-pregnant women with confirmed AIS with LVO in the anterior circulation, defined as per EU-US guidelines, with a <6 h window from onset of symptoms to ApTOLL administration, who are candidates to receive EVT treatment. For wake-up strokes, onset time will be considered as the time of symptoms first discovered.

Prior to the enrolment, all patients will undergo complete neuroimaging including non-contrast computerized tomography (NCCT), CT angiography, and CT perfusion (CTP). Only patients with an indication of EVT, based on NCCT findings (i.e., Alberta Stroke Program Early CT score, ASPECTS >5), will be evaluated as candidates for the APRIL study. Further neuroimaging inclusion criteria will be the presence of a single LVO at the level of the terminal internal carotid artery or the M1 or M2 segments of the middle cerebral artery and the identification of a favorable CTP profile as previously defined (18) to maximize the chances to identify a biological effect of the study drug. A predicted infarct core volume on CTP defined as cerebral blood flow (CBF) < 30% or diffusion-weighted imaging (DWI) between 5 and 70 ml should be identified with automated software (RAPID^®^ software) in order to be eligible for the APRIL study. After obtaining informed consent, the patients will be randomized to receive EVT + ApTOLL *vs*. EVT + placebo as shown in Figure 2. The study medication should be initiated after imaging acquisition and before EVT initiation (groin puncture). All patients will then be treated according to institutional protocols and national and European Stroke Organization (ESO) guidelines. At 90 days, the patients will undergo follow-up visit procedures.

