### 2.2. Objectives and endpoints

The aim of the APRIL study is to evaluate if ApTOLL is safe and shows any biological effect in AIS patients with LVO.

**Primary objective**: This study aimed to evaluate if the administration of ApTOLL i.v. at ascendant doses is safe and well tolerated as compared to placebo when administered with EVT in the AIS target population.**Secondary objectives**: Even though it is a unique study, the secondary objectives are different in the two study parts.

- Phase Ib:▪ To determine the pharmacokinetic profile of ApTOLL in patients with AIS, which is evaluated by the determination of ApTOLL levels in plasma and urine.▪ To select the two doses to be administered in Phase IIa according to their safety profile.▪ To provide an initial estimate of the biological effect of ApTOLL on the final infarct volume (measured by magnetic resonance image—fluid attenuated inversion recovery [MRI-FLAIR] at 72±24 h) and on pro-inflammatory biomarkers linked to AIS (baseline (pre-dose) and at the end of the infusion [up to 1 h], 6, 24, 48, and 72 h post-dose).

- Phase IIa:▪ To assess the biological effect of ApTOLL on the final infarct volume (measured by MRI-FLAIR at 72 ± 24 h) and on pro-inflammatory biomarkers linked to AIS (pre-dose and 6, 24, 48, and 72 h post-dose).▪ To determine the biological effect of ApTOLL as measured by the functional impairment (National Institute of Health Stroke Scale [NIHSS]) at 72 h or discharge (whichever occurs first) and disability (modified Ranking Score [mRS] at 90 d post stroke).

To achieve these objectives, the following endpoints will be evaluated:

**Primary endpoints**: Safety of ApTOLL when combined with EVT as determined by death, adverse events that occur during the study, physical examination, laboratory tests, recurrent stroke, and symptomatic intracranial hemorrhage (sICH).**Secondary endpoints**:

Mean final infarct volumes measured at 72 ± 24 h (MRI). In those cases where the MRI at 72 ± 24 h is missed, the last CT data available after ApTOLL administration should be considered.Proinflammatory markers in blood between study groups.Early clinical course [NIHSS; 72 h or discharge (whichever occurs first)].Long-term outcome (mRS; 90 days). In those cases where the mRS 90 days is missed, the last neurological assessment available after ApTOLL administration should be considered.Neuroimage proinflammatory biomarkers in MRI at 72 h and 90 d post-stroke (sub-study in some APRIL sites).

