#### 2.4.3. Transition from Phase Ib to Phase IIa

Before starting Phase IIa part of the study, and once safety data from the LPI in Phase Ib (SAD) is obtained (follow up 72 h visit from LPI last level), whole safety results will be evaluated to choose the most appropriate doses to be studied in Phase IIa part. The DSMB will evaluate the following safety parameters to select the two optimal doses to be studied in Phase IIa (Dose A, Dose B):

1. Regarding safety parameters in the stroke field, special attention will be paid to the occurrence of

Death: mortality data will be carefully collected for underlying causes.Intracranial hemorrhage (ICH) and hemorrhagic transformation (HT) result in new symptoms or worsening of the existing ones. ICH refers to any bleeding within the intracranial vault, including the brain parenchyma and surrounding meningeal spaces. HT represents the conversion of a stroke into an area of hemorrhage.Brain edema resulting in herniation and neurological worsening or death.Further potential AEs related to stroke to be carefully documented include the following:- Epileptic seizures.- Cardiac conduction disturbances, arrhythmias.- Effects on coagulation and fibrinolysis.- Hypotension/hypertension.- Hyperglycemia.- Hyperthermia.- Severe infections.- Deep vein thrombosis, pulmonary embolism, and venous thromboembolism.- Vomiting.- Anxiety, hallucinations, and agitation.

2. Regarding safety parameters related to the drug, special attention will be taken in relation to the following:

Complement activation: CH50 levels (50% hemolytic complement) and C3/C4 levels (Complement factors).Biochemistry: CK (Creatine Kinase) and CRP (C-Reactive Protein).Coagulation parameters: activated Partial Thromboplastin Time (aPTT), Prothrombin activity (PT), and International Normalized Ratio (INR).

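### Section 2.7 pools the Phase Ib patients used to choose the two doses into the comparison of those doses, so to the extent that selection followed observed events, the pooled safety contrast leans toward 'safe', by at most about 2 percentage points

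*Protocol article*

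**What the plan says.** Four statements in the protocol article bear on this.

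- **Selection.** Section 2.1 has a data safety monitoring board that is "unblinded to study groups will select 2 doses (A or B) to be tested in Phase IIa according to initial safety results". Section 2.2 lists this as a Phase Ib objective: "To select the two doses to be administered in Phase IIa according to their safety profile". Section 2.4.3 gives the criteria, beginning "The DSMB will evaluate the following safety parameters to select the two optimal doses to be studied in Phase IIa". They include death, intracranial haemorrhage, brain oedema, other adverse events, and complement, biochemistry and coagulation values, once the last Phase Ib patient has had the 72 h visit.
- **Primary endpoint.** Section 2.2: "Safety of ApTOLL when combined with EVT as determined by death, adverse events that occur during the study", followed by physical examination, laboratory tests, recurrent stroke and symptomatic intracranial haemorrhage.
- **Pooling.** Section 2.7: "Those patients enrolled in Phase Ib who received a placebo or the selected doses in phase Ib will be combined with Phase IIa patients". The stated purpose is more statistical power.
- **Justification.** Section 2.7 says that the gap between phases is minimal and that "the design, the follow-up, and data collection will be strictly the same in Phase Ib and Phase IIa parts of the trial", apart from pharmacokinetic and pharmacodynamic sampling.

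On sizes, the Figure 1 legend has "8 patients (6 ApTOLL: 2 Placebo) will be enrolled in 4 sequential ascending dose arms". Phase IIa has 119 patients at √2:1:1 (sections 2.1 and 2.4.4). The same legend reports that 0.05 and 0.2 mg/kg were carried forward.

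**The concern.** A dose that goes forward because its six Phase Ib patients did well has, on average, had some luck. Putting those six patients back into the arm carries the luck into the estimate. Here the selection criteria and the primary endpoint overlap heavily (deaths, haemorrhages, adverse events, laboratory values), so the effect would fall on the primary comparison. Placebo patients are not selected: all eight from Phase Ib are retained. The error therefore cannot cancel between arms, and it can only make ApTOLL look safer.

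The safeguards named in section 2.7 concern whether the two phases are comparable. None deals with selection. The pooling rule is an affirmative statement in the article, so this is not a detail merely left to the analysis plan.

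**Working it through.** **Inputs from the article.** Phase Ib: 4 doses × (6 ApTOLL + 2 placebo) = 32, that is 24 active and 8 placebo. Phase IIa: 119 patients.

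**Reproducing the article's allocation figures.** √2/(2+√2) = 0.414 and 1/(2+√2) = 0.293, matching the stated 0.41, 0.29 and 0.29. Times 119 this gives 49.3, 34.9 and 34.9, or about 49:35:35.

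**Combined set.** 119 + 12 + 8 = 139 of 151 patients: about 35 + 6 = 41 per selected dose and 49 + 8 = 57 on placebo. Phase Ib supplies 6/41 = 14.6% of each active arm.

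**Assumptions, since the article gives neither event rates nor a ranking rule.** All four doses share one true event rate, and the two doses with fewest events among their six patients are kept, ties at random. Of the rules examined at equal rates, this one gives the largest bias.

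**Formula.** Bias of the pooled arm = (expected rate in a selected Phase Ib cohort − true rate) × 6/41. Because placebo is unselected, the risk difference shifts by the same amount. SE of the pooled difference = √[p(1−p)(1/41 + 1/57)].

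| True rate | Selected Phase Ib cohorts | Bias there | Bias of pooled arm | SE of pooled difference | Bias/SE |
|---|---|---|---|---|---|
| 5% | 0.5% | −4.5 | −0.7 | 4.5 | 0.15 |
| 10% | 2.7% | −7.3 | −1.1 | 6.1 | 0.17 |
| 15% | 5.9% | −9.1 | −1.3 | 7.3 | 0.18 |
| 20% | 9.6% | −10.4 | −1.5 | 8.2 | 0.19 |
| 30% | 17.9% | −12.1 | −1.8 | 9.4 | 0.19 |
| 50% | 36.7% | −13.3 | −1.9 | 10.2 | 0.19 |

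(Biases and SEs in percentage points.) At 15%, for example: (5.9 − 15) × 6/41 = −1.3.

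**Other selection rules.** With a threshold rule (a dose with 3 or more events in 6 patients, and all doses above it, count as unsafe; the two highest remaining doses are kept), simulated bias was 0.1 to 1.0 points, for rates starting at 10% or 20%, either flat or rising with dose. With selection unrelated to events, it was zero. The Phase IIa-only estimate had no bias in any scenario.

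**Effect of the 72 h cut-off.** If half of all events were visible when doses were chosen (an assumption), the worst-case bias at 15% falls from 1.3 to 0.8 points.

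**Precision.** SE ratio, pooled to Phase IIa only: √[(1/41 + 1/57)/(1/35 + 1/49)] = 0.925. Dropping Phase Ib therefore raises the SE by 1/0.925 − 1 = 8%.

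**Stratifying by phase.** The stratum weights are 35×49/84 = 20.42 (Phase IIa) and 6×8/14 = 3.43 (Phase Ib). The variance factor is 1/(20.42 + 3.43) = 0.0419, the same as unstratified to that precision. The Phase Ib weight is 3.43/23.85 = 14.4%, against 14.6% unstratified, so the bias at 15% stays at −1.3 points.

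**Design in the two phases.** Phase Ib (sections 2.1 and 2.4.2): sequential ascending cohorts, 3:1 active to placebo. Phase IIa (sections 2.1 and 2.4.4): three parallel arms, √2:1:1 placebo to dose A to dose B. These are not the same design.

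**The case against.** The strongest reply is that the worst case is not what happened and that pooling is still worthwhile.

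- Nothing says the board ranked doses by event count. Section 2.7 assumes that any dose above an unsafe one is also unsafe. Since 0.2 mg/kg was kept and 0.1 mg/kg was not, 0.1 mg/kg was not, on the plan's own logic, dropped as unsafe. This stands. It makes a bias well below the table plausible, though it does not show that observed events played no part.
- Selection needed data only to 72 h, whereas adverse events are collected to day 90 (Table 2). This stands and reduces the bias for later events.
- Even in the worst case the pooled estimate has the lower root-mean-square error: 4.3 against 4.8 points at 5%, 7.2 against 7.9 at 15%, 9.3 against 10.1 at 30% and 10.2 against 11.1 at 50%. This stands too. Leading with Phase IIa alone would trade precision for unbiasedness, and the calculation does not require it.
- Section 2.7 gives power as the purpose and does not name safety. True, but it exempts no endpoint, so the rule as written covers safety.

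A reader might also infer that the 12 of 94 ApTOLL patients on the two unselected doses (24 in Phase Ib plus about 70 in Phase IIa) disappear from the safety data. The article does not say so. It says only who is combined; the board reviews every dose level, and the analysis plan with its tables and listings is not shown.

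**Conclusion.** The point holds in conditional form. The plan selects doses on Phase Ib safety, makes safety the primary endpoint, and pools the selected patients with no endpoint exempted. To the extent that selection followed observed events, the pooled safety contrast leans toward 'safe', by at most about 0.7 to 1.9 points for assumed true rates of 5% to 50%, and under 0.2 SE throughout. That bound rests on equal true rates and keeping the two doses with fewest events. Milder rules and events after 72 h bring it down, and selection that ignored events brings it to zero.

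The stronger reading, that the primary safety estimate is known to be biased or that the comparison misleads, is not supported: the actual selection rule is not given, and the shift is small against sampling error. The statement that the design is identical in both phases is contradicted by sections 2.1, 2.4.2 and 2.4.4, but that is a matter of wording and adds nothing to the selection bias.

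**What to change.** 1. For safety endpoints, prespecify the concurrently randomised Phase IIa-only comparison (about 49:35:35) beside the pooled one, and state that the pooled estimate includes the data used to select the doses. Cost: one further analysis, with an SE about 8% larger (7.9 against 7.3 points at a 15% event rate), and no extra patients.
2. Stratify any pooled analysis by phase, or include phase as a covariate, to handle differences between phases. The cost in variance is negligible. This should not be presented as a remedy for selection bias, which it leaves unchanged.
3. In section 2.7, replace the claim of an identical design with an accurate one: follow-up and data collection are the same apart from the listed sampling, while Phase Ib uses sequential 3:1 cohorts and Phase IIa parallel √2:1:1 arms. Cost: wording only.

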## 3. Discussion

Stroke is a devastating and debilitating disease with limited therapeutic options. To date, European and US guidelines for stroke treatment only recommend the use of thrombolytics and/or EVT. However, revascularization therapies alone appear to be insufficient for a substantial proportion of patients, and the combination of recanalization with neuroprotectants is emerging as a promising strategy to improve the outcomes of patients who suffer a stroke (8–11). This possibility to reestablish cerebral flow with EVT generates a new scenario for testing drugs with potential neuroprotective effects. In fact, Nerinetide (NA-1), a neuroprotectant focused on the inhibition of PSD-95 implicated in the excitotoxic process developed after stroke, has been shown to improve outcomes in a subpopulation of patients with AIS when administered in combination with EVT [ESCAPE-NA1 trial (19)].

In this context, we propose the APRIL clinical trial protocol (EudraCT: 2020-002059-38), a clinical study to assess the safety and biological effect of ApTOLL, an anti-inflammatory drug with proven neuroprotective effects in preclinical models. The study will focus on patients with AIS who are candidates for EVT (with or without thrombolysis) within 6 h from stroke symptoms onset to ApTOLL administration with the objective of ensuring recanalization.

Patients undergoing EVT replicate transient ischemic models and are therefore ideal candidates for neuroprotection studies since the expected recanalization rates are around 85-90% offering a homogeneous population with measurable infarct core, tissue at risk, and occlusion location that will be recanalized in most cases within few hours after admission. The profile of the patient candidates for EVT however might be different in the early (0–6 h) vs. the late (6–24 h) time window and, also, there are patients who still show salvageable brain tissue despite a long time of ischemia (usually called slow progressors) and patients in whom the ischemic brain tissue shows complete irreversible ischemic changes soon after symptom onset (fast progressors). In order to maximize the chances to observe differences in the measured outcomes between patients who will receive ApTOLL vs. placebo, patients presumed to dilute the potential treatment effect of ApTOLL are attempted to be excluded. The inclusion criteria of the APRIL study (combining time from symptom onset < 6 h and an identifiable infarct core on admission CTP) are designed to include predominantly “fast progressors” and exclude those patients in which the final infarct volume is expected to be minimal or very large with the standard treatment.

The rationale to enroll patients with moderate infarct core (5–70 cc) comes from Olivé-Gadea et al. (20). It is not infrequent that patients suffering a severe stroke that undergoes EVT will experience a dramatic clinical recovery with no residual or very little final infarct or neurological deficit. Among this group of patients, a neuroprotective drug will not be able to show its benefits and therefore including these patients in such a trial may only dilute any potential neuroprotective effect (ceiling effect). On the other hand, in those patients that will develop very large final infarcts, a potential relative reduction of final infarct size induced by the neuroprotective drug may be insufficient to induce a measurable reduction in a neurological deficit. According to this theory, patients forecasted to develop a moderate infarct size after receiving EVT would be the optimal target population in which a neuroprotectant may have the highest potential to show its clinical and radiological benefits. CTP has shown to be a valuable tool to predict on admission the final infarct volume. In particular a baseline CBF<30% showed the best correlation with final infarct volume in those patients that will achieve a significant recanalization and therefore can be considered an adequate surrogate of the infarct core on admission.

In conclusion, there is a new opportunity for neuroprotectants like ApTOLL to demonstrate their activity in combination with EVT. However, building on learning from prior treatment successes and failures, there is also a need for selecting the appropriate AIS patients' population to guarantee that the neuroprotective effect of the drug is made evident. Therefore, the APRIL study aims to replicate the promising results observed in preclinical models of transient ischemia and demonstrate the safety and efficacy of ApTOLL in the defined target population of patients with stroke treated with EVT, in whom ApTOLL has the theoretically highest chances to show positive clinical and radiological effects.

Supported by all this rationale, the APRIL trial has been designed using a novel approach to test neuroprotective drugs focusing on selecting patients with LVO and moderate infarct volumes (core between 5 and 70 cc), using appropriate image techniques (CTP and MRI) and assessing the appropriate endpoints.

The results of the APRIL trial will be published within 1 year from the last follow up of the last patient enrolled in the trial.

